## Methods

### Study design

The effectiveness and fidelity of Houvast are investigated by means of a quasi-experimental research design with two groups and one baseline and two follow-up measurements (Figure 1). Both the intervention group and the control group (‘care as usual’) consist of Dutch services for homeless youth which deliver ambulatory and/or residential care. The services are randomly allocated to the intervention (*n* = 5) or control group (*n* = 5). Stratified randomization is used to ensure that services which deliver ambulant and/or residential care are equally distributed among each group. Randomization of homeless youths was not feasible since entire teams were trained prior to the baseline measurement in the strengths based method. Hence, a quasi-experimental research design is the best feasible design.

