### Sample size and power calculation

To our knowledge no research among homeless youth has been carried out that used this quality of life instrument [39] to measure quality of life as the primary outcome measure. In comparable research among youths, in which a different instrument was used [75], an effect size of .95 was observed. Compared to baseline measurement, youths in the experimental group reported an increase in general life satisfaction of 6.45 (SD=5.89) at nine-month follow-up while controls reported a decrease of −2.25 (SD=11.61). Given that the setting and focus of the present study are different compared to Ferguson and Xie [75], a more conservative effect size was chosen. To calculate the required sample size, a mean improvement in the subjective quality of score of 0.74 (SD=1.48) is assumed. To detect this difference with 80% power (α = .05, two-sided), each group should comprise 63 participants. Considering potential loss of power due to clustering of data in services, power analyses revealed that at least 15–20 participants in each service (ICC = .05) are needed. Thus, taking a maximum of 30% attrition over time into account, 251 participants at baseline, and 178 participants at T1 are required.

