### Analyses

1) Differences in baseline characteristics (age, gender, education, nationality and ethnicity) between the intervention and control group will be checked by using Chi-square tests, Student’s t-tests and ANOVA's.

2) To examine if the Houvast method proves to be effective or not and to examine additional factors associated with quality of life of homeless youths, a two-level multilevel regression analysis will be used. Since data is clustered – youths are ‘nested’ in services – the analysis will be adjusted for the cluster effect at ‘service’ level. Analyses will be adjusted for potential confounders, such as gender, age, ethnicity, intellectual disability, duration of homelessness and model fidelity.

3) To assess the degree of consensus on the working relationship satisfaction between professionals and youths, a one-with-many design with multilevel analysis will be used. This design addresses the problems associated with non-independence and it accounts for interdependence between professionals and youths.

4) Regarding the fidelity assessment of the strengths based method of each service, all sources (e.g. questionnaires, interviews, observations) will be analysed and by averaging the scores on ten indicators a total score on a 5-point scale will be obtained, whereby a score of 4 reflects a sufficient model fidelity. The total score will also be used as a covariate when examining the effectiveness of Houvast.

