Some limitations may be mentioned as well. First, due to the complex and unpredictable situation of homeless youth, it may be difficult to motivate them to participate in the follow-up interviews. Most youths leave the service within nine months and locating them to make an appointment for a final interview requires a large investment of researchers. By increasing the financial compensation for their time and effort to complete the interviews, they will hopefully remain motivated. Second, even though youths are interviewed for the first time during the first two weeks after entering the service, there is a small possibility that they were influenced in their scoring on the baseline measurement by whether they entered an experimental or a control service. We will inspect the baseline scores of both groups on significant differences in quality of life and the secondary outcomes, the last follow-up measurement will be conducted at nine months after baseline. Even though it is unique to follow homeless youths for this extensive period of time, a longer time span in which their recovery (or not) would have become more apparent would have been ideal. However, due to practical and financial constraints this was not feasible in the present study.

If the Houvast method proves to be effective in improving the quality of life of homeless youths, the study has strong practical relevance as the quality of work within services for homeless youth could be improved and more professionalized.

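### The effectiveness model does not name the baseline quality-of-life score or the care-type stratum as covariates; both should be fixed in advance, the baseline score regardless of any baseline test

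*Protocol article*

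**What the plan says.** In the protocol article, item 2 of the Analyses section says that "a two-level multilevel regression analysis will be used", with youths nested in services. On covariates it says: "Analyses will be adjusted for potential confounders, such as gender, age, ethnicity, intellectual disability, duration of homelessness and model fidelity". The T0 score of the outcome and the type of care are not in that list.

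Type of care did shape the allocation. The Study design section says: "Stratified randomization is used to ensure that services which deliver ambulant and/or residential care are equally distributed among each group". It describes the study as a "quasi-experimental research design with two groups and one baseline and two follow-up measurements", so a T0 score is planned for every youth who enters.

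The one stated use of the T0 outcome scores is in the limitations part of the Discussion: "We will inspect the baseline scores of both groups on significant differences in quality of life and the secondary outcomes". Nothing says what follows from that inspection, or that the scores enter the model in any case.

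**The concern.** A baseline measurement of the outcome is usually among the strongest predictors of its follow-up value. Leaving its role open has two costs.

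The first is bias and discretion. With five services per arm, a prognostically important imbalance can arise and still be non-significant, so a significance check does not show whether adjustment is needed. Because the covariate list is open, the decision to adjust could also be taken after the baseline data are seen. Baseline differences here need not be pure chance. The Study design section says that teams were trained before the baseline measurement, and the Procedure section says that professionals in those services approach the youths. The Discussion itself grants that the service a youth entered may influence T0 scores.

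The second is precision. Once clustering is counted, the trial is below its 80% target on the article's own figures (see the working), and the T0 score is an inexpensive way to recover some of that.

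The stratum raises a separate point. A factor judged important enough to stratify ten services on would normally be carried into the analysis, and item 2 does not mention it.

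**Working it through.** **Inputs from the article (Sample size and power calculation; Study design).** Difference 0.74 and SD 1.48, two-sided α .05, 80% power, ICC .05, 178 participants at T1, five services per arm.

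**Assumptions.** The article gives no T0–follow-up correlation r; the range 0.3–0.6 is used. SD 1.48 is read as the SD of the follow-up score. Services are of equal size.

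**The plan's own figure.** n per group = 2 × [1.48 × (1.960 + 0.842) / 0.74]² = 62.8, so 63. This agrees with "To detect this difference with 80% power (α = .05, two-sided), each group should comprise 63 participants".

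**Unadjusted precision at 178 analysed (89 per arm).** Total variance is 1.48² = 2.190. Between services: 0.05 × 2.190 = 0.1095. Within services: 0.95 × 2.190 = 2.081.

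SE = √[2 × (0.1095/5 + 2.081/89)] = 0.301, and 0.74/0.301 = 2.46. Power is 69% by the normal approximation. It is 58% by the noncentral t with 8 df (ten services minus two arms).

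**Adding the T0 score.** Within-service variance is multiplied by 1 − r². In the favourable scenario, between-service variance is multiplied by the same factor.

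| r | 1 − r² | Within services only: SE; power normal / 8 df | Both levels: SE; power normal / 8 df |
|---|---|---|---|
| 0 (no adjustment) | 1 | 0.301; 69% / 58% | 0.301; 69% / 58% |
| 0.3 | 0.91 | 0.294; 71% / 60% | 0.287; 73% / 62% |
| 0.5 | 0.75 | 0.281; 75% / 64% | 0.261; 81% / 70% |
| 0.6 | 0.64 | 0.272; 78% / 67% | 0.241; 87% / 77% |

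**If the outcome is change from baseline.** With equal SDs at both times, a change score has variance proportional to 2(1 − r) and an analysis of covariance has variance proportional to 1 − r². The ratio is (1 − r²)/[2(1 − r)] = (1 + r)/2, which is 0.65 at r = 0.3, 0.75 at 0.5 and 0.80 at 0.6. Covariance adjustment still helps, but the power figures in the table do not carry over directly, because 1.48 would then be the SD of change.

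**Adding one stratum term alone.** This leaves 7 df and reduces between-service variance by the share that care type explains.

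| Share of between-service variance explained | Power (t, 7 df) | Without the term (t, 8 df) |
|---|---|---|
| 0% | 56% | 58% |
| 25% | 62% | 58% |
| 50% | 68% | 58% |

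**The case against.** The strongest objection is that this is a condensed article and that its covariate list is introduced as examples. A reader might infer that the T0 score and care type are excluded from the model, or that the analysis ignores how services were randomised. The text supports neither: it does not name the two variables, and it does not rule them out. A full protocol or analysis plan may list them. This objection limits the claim, but it does not remove the point. The article does state a plan for baseline scores, namely an inspection for significant differences, and that approach is weak whatever else is listed.

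Second, the T0 score may already be used. The sample size section assumes "a mean improvement in the subjective quality of score of 0.74 (SD=1.48) is assumed", and the earlier study it draws on is reported as change from baseline. A change-score outcome is therefore possible, though not stated. In that case the T0 score would not be missing, and the point would be one of efficiency, with the variance ratio (1 + r)/2.

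Third, the size of the gain depends on an assumed correlation. It also depends on whether T0 explains differences between services as well as between youths. At r = 0.3 with a within-service gain only, power rises by about 2 percentage points. It would be too strong to say that adjustment is certain to recover most of the power lost to clustering.

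Fourth, it is tempting to say that omitting the stratum wastes precision. With ten services that is not assured: a stratum term that explains nothing lowers power from 58% to 56%.

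Finally, a reader might infer that a two-level model is wrong because there are two follow-ups and no level for occasions. That would follow only if T1 and T2 were modelled jointly, which the article does not say. Separate two-level models at T1 and T2 fit the text, so this is not part of the point.

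**Conclusion.** The point holds as a request to prespecify. Item 2 does not name the T0 score or care type, and the only stated handling of baseline outcome scores is a significance check, which is not a sound basis for deciding on adjustment with ten services.

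For the T0 score, the gain is positive at every assumed r. It ranges from about 2 percentage points (r = 0.3, within services only) to about 18–19 points (r = 0.6, both levels). Even so, power reaches 80% only in the more favourable cases: by the normal approximation at r = 0.5 and above if both levels benefit, and nowhere in the range with 8 df. These figures rest on the assumed r and on reading 1.48 as the SD of the follow-up score.

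For care type, the case is that the analysis should follow the stratified allocation. Its effect on power may be slightly negative or moderately positive (56–68% against 58%). No figure stated in the article is disputed by this point.

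**What to change.** Add to item 2 of the Analyses section that the primary model always includes, as fixed effects:

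- the T0 score of the outcome being analysed, regardless of any test of baseline differences;
- type of care as used in the stratified randomisation.

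The same item should say whether the outcome is the follow-up score or change from baseline. The inspection of baseline scores can stay as description, but it should not decide the model.

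The cost is wording only, because T0 scores are already being collected and type of care is known for each service. There are two downsides to record. T0 may be taken up to two weeks into care, so it may already carry a little of the effect, and adjusting for it could remove that part. The stratum term uses one of the 8 between-service degrees of freedom.

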## Discussion

There is a substantial need for an evidence-based method that is effective in addressing the specific needs of homeless youths [21]. The present study aims to fill this gap by examining the effectiveness and fidelity of the strengths based Houvast method.

This study possesses several strengths. First, the study is unique because it examines the effectiveness of a strengths based intervention among homeless youth. Second, this study will provide in-depth information about the development and recovery of homeless youths within a critical period of their lives. Third, the study also assesses the fidelity of the working method which has, to our knowledge, never been done before in intervention studies among homeless youth. A possible explanation for not finding effectiveness can be poor implementation of the Houvast method, resulting in low intervention fidelity. Therefore, in this study much attention is paid to implementation activities for both professionals and (team) managers. Furthermore, internal coaches at each service are established to supervise the implementation process. So far, the implementation activities have generated much enthusiasm and motivation among professionals, team managers and other stakeholders. Fourth, this study not only provides a framework for fidelity measurement but also results in a quality framework that can be used in other organizations for homeless youth. Fifth, the Houvast method could be improved based on the results of the effectiveness and fidelity measurements and will give organizations and also policy makers, for example in municipalities or ministry departments, handles for adjusting or changing their policies on homeless youths.

In addition, this study has also considerable methodological strengths as it is the first time that a larger sample (*n* = 251 at baseline) of homeless youths will be followed up for a period of nine months within an intervention and a control group. Youths will be interviewed by trained interviewers who are unaware of the randomization of services to the intervention of control group which minimizes potential interview bias.

Some limitations may be mentioned as well. First, due to the complex and unpredictable situation of homeless youth, it may be difficult to motivate them to participate in the follow-up interviews. Most youths leave the service within nine months and locating them to make an appointment for a final interview requires a large investment of researchers. By increasing the financial compensation for their time and effort to complete the interviews, they will hopefully remain motivated. Second, even though youths are interviewed for the first time during the first two weeks after entering the service, there is a small possibility that they were influenced in their scoring on the baseline measurement by whether they entered an experimental or a control service. We will inspect the baseline scores of both groups on significant differences in quality of life and the secondary outcomes, the last follow-up measurement will be conducted at nine months after baseline. Even though it is unique to follow homeless youths for this extensive period of time, a longer time span in which their recovery (or not) would have become more apparent would have been ideal. However, due to practical and financial constraints this was not feasible in the present study.

If the Houvast method proves to be effective in improving the quality of life of homeless youths, the study has strong practical relevance as the quality of work within services for homeless youth could be improved and more professionalized.
